#### **9.4 Multivariable analysis**

In case the groups differ on baseline values or other possibly confounding variables, the difference in change in  $\text{VO}_{2\text{peak}}$  level between baseline and 6 months between the intervention groups will be tested by means of linear mixed models analysis with centre as a random effect in which we will control for relevant confounders by adding covariates to the model. We will conclude a statistical significant difference in change in  $\text{VO}_{2\text{peak}}$  level between the *mCR* and control group when the two-sided p-value of the test statistic after adjustment for confounders is less than 0.05.

#### **9.5 Population**

The intention to treat population is used for analysis of the primary and secondary endpoints. All patients will be analysed in the group they are randomised to and whether or not they completed the *mCR* programme according to protocol.

#### **9.6 Missing values**

We will present numbers and percentages of missing values. Missing values will be analysed in order to see if these missing values are systematically different between both groups (*mCR* and control group) or whether they are related to baseline values or values on earlier time points. In case that the occurrence of missing values is systematically different between groups, or is related to other relevant variables, multiple imputation methods will be used to calculate parameter estimates as a sensitivity analysis.

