#### 5.4 Sample size calculation

In order to assess the effects on sustained physical fitness after participation in the *mCR* programme it was determined that an inclusion of 119 patients per group would be sufficient to examine the aim of this study.

This is based on the expected difference in increase in  $VO_{2peak}$  level of 3.0 ml/kg/min at 6 months between the control and intervention group with an estimated standard deviation of 5 ml/kg/min in the intervention group and 6 ml/kg/min in the control group. Assuming 80% power and 5% two-sided significance level ( $\alpha=0.05$ ), the sample size ( $n$ ) required to achieve a probability of 80% of detecting a difference in an increase  $VO_{2peak}$  level between two independent groups is  $n=55$  per randomisation group. Since patients from different centres (countries) will be pooled in the analysis, we will apply an adjustment for dependency of the observations to calculate the sample size, based on an estimated intraclass correlation coefficient (ICC) for the study centres.

The ICC is the proportion of the total variance which is between the centers rather than within centres. An ICC of 0.05 is used in the sample size calculations. After adjustment for the ICC the sample size is  $N=83$  per group. Based on 30% withdrawal we aim for a group size of  $n=119$  per randomisation group ( $n=238$  in total). Six centres will participate in the RCT so we will aim at including approximately 40 patients per centre. As this is a cooperative trial, centres may recruit more patients than this recruitment goal. When one centre starts to dominate enrolment however, recruitment might need to be capped. The total sample size ( $n=238$ ) would be sufficient to detect a clinically and physiologically relevant change in peak oxygen consumption, despite a 30% dropout.

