### 9.2 Primary analyses

The primary endpoint is the change in  $VO_{2peak}$  level between baseline and at 6 months. It will be tested whether this change is different in the *mCR* and the control group by means of linear mixed models with the intervention as a fixed effect. The effect of centre on the outcome is modelled with a random effect. In the analyses we will adjust for the baseline value of  $VO_{2peak}$ . When necessary the outcome variable will be transformed to obtain a normal distribution. The null hypothesis is that there is no difference in mean change in  $VO_{2peak}$  level between the randomised groups. The alternative hypothesis is that the mean

change in  $VO_{2peak}$  level differs between the randomised groups. A two-sided p-value of less than 0.05 will be considered to be statistically significant.

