#### 4.7 Missing data

All collected data will be used in the data analysis, also data from the patient who discontinue the study until the time of study discontinuation. Missing data will be reported overall and by intervention and centre. We will describe patterns in missing data. We will analyse whether missing data are systematically different between both groups (*mCR* and control group) or whether they are related to baseline values or values on earlier time points. In case that the occurrence of missing values is systematically different between groups, or is related to other variables, multiple imputation methods will be used to calculate parameter estimates for sensitivity analysis.

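### With 30% withdrawal planned, no analysis tests how the T1-T0 VO2peak result depends on assuming that patients without a T1 test resemble those with one

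*Combined protocol and SAP*

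**What the plan says.** Protocol 5.4 and SAP 3 build the sample size on a withdrawal allowance: "Based on 30% withdrawal we aim for a group size of" 119 per arm.

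Protocol 9.2 and SAP 5.1 analyse the change from T0 to T1 in a linear mixed model with arm as a fixed effect and centre as a random effect. On baseline, Protocol 9.2 says "In the analyses we will adjust for the baseline value of" VO2peak.

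On missing values, Protocol 9.6 first compares missingness between arms and against baseline and earlier values. It then makes imputation conditional: "In case that the occurrence of missing values is systematically different between groups, or is related to other relevant variables, multiple imputation methods" serve as a sensitivity analysis. SAP 4.7 has the same condition, after which "multiple imputation methods will be used to calculate parameter estimates for sensitivity analysis". Neither section specifies an imputation model, a delta adjustment, a reference-based rule or a tipping point.

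SAP 5.1 takes a different line for the primary outcome. It states that the mixed model copes adequately with missing data, and on that ground excludes multiple imputation and any other missing-data method.

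**The concern.** A sensitivity analysis for missing data should show how far the conclusion rests on an assumption the data cannot check. Here that assumption is that, given arm, centre and baseline, patients who did not return at six months changed as much as those who did. The condition in Protocol 9.6 and SAP 4.7 uses observed variables only. If patients leave because of the response that is never measured, the check sees it only through weak correlates or through an imbalance in dropout between arms. If imputation is run in its standard form, it again assumes missing at random.

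This matters more than usual because the trial is open label (Protocol 7.5), the programme asks for exercise five days a week (Protocol 6.1), and about three patients in ten may lack the primary outcome. Leaving could plausibly be related to response in either arm. As planned, a positive or a null VO2peak result could rest on the assumption without any reported analysis showing it. Read with SAP 5.1, the primary endpoint may have no missing-data sensitivity analysis at all.

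**Working it through.** **Inputs from the documents** (Protocol 5.4, repeated in SAP 3): "Assuming 80% power and 5% two-sided significance level"; a difference in increase at a "level of 3.0 ml/kg/min at 6 months between the control and intervention group"; "estimated standard deviation of 5 ml/kg/min in the intervention group and 6 ml/kg/min in the control group"; "An ICC of 0.05 is used in the sample size calculations"; 30% withdrawal, not split by arm.

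**The plan's own figures.**
- Root-mean-square SD = √((25 + 36)/2) = 5.52. The normal formula gives 54 per arm. The t-test gives 55 (power 0.806), as stated.
- The clustering step to 83 is taken as stated. It implies a design effect of 83/55 = 1.51.
- 83/(1 − 0.30) = 118.6, so 119 per arm, as stated.
- 0.30 × 119 = 35.7, so about 36 patients per arm may have no T1 value.

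**Size of the dependence.** Suppose mCR patients without T1 did worse by δ than the model implicitly assumes, and control leavers are missing at random. Then

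effect over all randomised = completer effect − (share missing in mCR × δ).

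- Completer effect 3.0, 30% missing, δ = 3.0 (leavers gain no more than controls): 3.0 − 0.3 × 3.0 = 2.1 ml/kg/min.
- With 20% or 40% missing in mCR: 2.4 or 1.8.
- SE with 83 per arm = √(61/83) = 0.857, or 0.857 × √1.51 = 1.053 with the plan's design effect. For an observed 3.0, significance is lost at δ = (3.0 − 1.96 × SE)/0.3 = 4.4 or 3.1. For an observed 2.5, it is lost at 2.7 or 1.5.

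**Simulation of the T1-T0 model with no true effect.** Settings: 119 per arm, SDs of change 5 and 6, 30% missing in each arm. Assumed: baseline SD 5, correlation of change with baseline −0.3.

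| Who leaves selectively | Dropout odds ratio per SD of worse response | Mean estimate (ml/kg/min) | Falsely significant for mCR (nominal 2.5%) |
|---|---|---|---|
| mCR only | 1.5 | +0.50 | 9.5% |
| mCR only | 2 | +0.86 | 18.9% |
| mCR only | 3 | +1.22 | 34.4% |
| Both arms | 2 | −0.21 | – |
| Control only | 2 | −1.06 | – |

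**How often the condition is met.** I took it as a test of missingness by arm plus a test of baseline by missingness. In the mCR-only scenarios with 30% missing in each arm it is met in 12% to 19% of trials, so it stays silent in more than 80%. With unequal dropout at odds ratio 2 (36% v 24%, or 40% v 20%) it is met in 59% to 94%.

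**T2-T0.** The planned T2-T0 model (Protocol 9.3, SAP 5.2) adjusts for baseline only. Assume 30% missing at T2, mCR dropout odds 2 to 3 times higher per SD of worse observed T1 change, and a T1-T2 residual correlation of 0.5 to 0.7. With no true effect, that model is biased by +0.42 to +0.90. Imputation that includes the T1 value brings the estimate to about zero.

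**Other planned analyses.**
- The per-protocol set (SAP 4.2.2) requires adequate tests at T0, T1 and T2, so it excludes these patients.
- The repeated-measures model (Protocol 9.3, SAP 6) uses all visits but also rests on missing at random.
- SAP 13.2 models drop-out as an outcome and does not feed it into the VO2peak comparison.
- Patients who leave the study are followed for events and care use, not VO2peak (Protocol 7.10).

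**The case against.** The strongest reply is that the plan is not blind to dropout and that planned imputation can do real work. Several parts of this stand.

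- **Imputation is not always redundant.** A reader might infer that the planned imputation can only repeat the main estimate. That does not hold at T2: the check covers earlier time points, nothing limits the imputation model to arm and baseline, and using T1 removes bias that the T2-T0 model leaves. The repeated-measures model can recover some of the same information.
- **The condition is not inert.** A reader might infer that it is met only by chance. That depends on equal dropout in the two arms. The documents do not split the 30%, and with unequal dropout the condition is often met.
- **The direction is not given.** A reader might infer that the bias must favour mCR. The documents say nothing about why patients leave either arm, and the same mechanism in controls reverses the sign.
- **Stopping mCR is not the same as missing data.** Patients are analysed as randomised whether or not they complete the programme (Protocol 9.5, SAP 4.2.1), and those taken off mCR after a reintervention with a new indication are still tested (Protocol 7.9). The 30% is an allowance, and the 2.1 is an illustration.
- **Drop-out is examined.** SAP 13.2 covers its reasons and predictors, so it would be wrong to say that nobody looks at who left.
- **Missing at random is an inference.** The documents do not use the term. It follows from the model as specified and from the absence of any other imputation rule.

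None of this supplies an analysis of the T1-T0 effect under a different assumption about the missing T1 values. When imputation is run, it still assumes missing at random unless a departure is specified.

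**Conclusion.** The point holds for T1-T0 VO2peak: no planned analysis shows how the treatment effect changes if patients without a T1 test differ from those with one. Protocol 9.6 and SAP 4.7 also conflict with SAP 5.1 on whether the primary outcome gets any imputation.

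Under the stated assumptions, the undetected bias with no true effect is about +0.5 to +1.2 ml/kg/min when poor responders leave mCR only, with false wins for mCR in about 10% to 34% of trials. It is about −0.2 when poor responders leave both arms and about −1.1 when they leave control only (odds ratio 2 in both cases). These figures show what the plan could miss and do not forecast what will happen. They rest on an assumed dropout mechanism, an assumed baseline SD and correlation, and all 30% lacking T1.

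The documents do not support concluding that the primary analysis is invalid or biased towards mCR. The planned mixed model is a reasonable main analysis. This is a change that should be made, at low cost.

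**What to change.** 1. Reconcile Protocol 9.6, SAP 4.7 and SAP 5.1 so that they say the same thing about the primary outcome. Amending 9.6 and 4.7 alone would leave 5.1 forbidding the new analysis.
2. Keep the planned mixed model as the main analysis. Keep the description of missingness, but do not use it to decide whether a sensitivity analysis runs.
3. Always run one missing-not-at-random sensitivity analysis for T1-T0 VO2peak. Either of these would do:
   - a delta-adjusted tipping-point analysis, shifting imputed values in steps (for example 0.5 ml/kg/min) in each arm separately and in both, and reporting the shifts at which the conclusion changes; or
   - reference-based imputation, with missing mCR values drawn from the control distribution given baseline.
4. Do the same for T2-T0 with the T1 value in the imputation model. Always run the missing-at-random imputation with T1 there too.
5. Extending this to the other continuous outcomes is optional.

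The cost is SAP wording and some programming on data already being collected. The downside is that a less favourable supportive estimate may have to be reported beside the main result.

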## **10. ETHICAL CONSIDERATIONS**

### **10.1 Regulation statement**

All patients participating in the clinical study are extensively informed with the help of the patient information about the planned examinations as well as their benefits and risks. The patient consents to participating in the study and the forwarding of his or her data by signing the respective form.

A central vote is applied for at the ethics committee responsible for the principal investigator. The study can only begin after a positive vote.

All examinations are performed by the site investigator or a co-investigator authorised by him or her in accordance with the Declaration of Helsinki (see APPENDIX II), the corresponding national laws, and according to the current state of science and technology.

Any patient-related information that reaches the sponsor during this study is treated confidentially. Only specially authorised and trained personnel are given access to the study data. The stipulations recommended in the Declaration of Helsinki and required in national laws regarding data protection comply with by all involved parties.

### **10.2 Recruitment and consent**

Patients will be recruited from the department of Cardiology of each participating centre. A physician or nurse specialised in CR will screen the patients and decide whether they can be a potential participant in this study. All patients who participate in this study have an adequate insurance coverage after weighing all risks (patient insurance). All patients participating in the clinical study are screened and extensively informed by a physician or nurse specialised in CR with the help of the patient information about the planned examinations as well as their benefits and risks. The patient consents to participating in the study and the forwarding of his or her data by signing the respective form.

Any patient-related information that reaches the sponsor during this study is treated confidentially. Only specially authorised and trained personnel are given access to the study.

Patients, who are capacitated, meet the inclusion and exclusion criteria and sign the informed consent, will be considered enrolled in the study. In case of incapacity of the patient, he or she is not able to participate in the study. Informed consent forms have to be in compliance with the latest Declaration of Helsinki. The patient shall be given a copy of the signed informed consent form, and the original shall be kept in the centre's regulatory file.

### **10.3 Benefits and risks assessment, group relatedness**

At all participating centres, there is a long-standing tradition in performing non-invasive testing as used in this present study. All procedures are performed routinely at the departments and have been accepted by the ethics committee in numerous previous applications in healthy as well as various patients groups.

Non-invasive cardiac testing procedures in this study are not related to any potential risk for the participant. Maximal ergometer tests will be performed at the hospital under supervision of highly qualified personnel.

A possible complication of venipuncture is a hematoma, which is induced in ~5% of all cases. To prevent complications, an experienced professional will perform the blood withdrawal and sufficient pressure will be provided after withdrawal of the needle. As patients are carefully instructed beforehand and individually coached by telephone on their physical progress during the first 6 months of the study we expect no potential risk for them to exercise in their home environment.

Taken together, our study involves minimally and non-invasive measures, whilst the *mCR* programme is believed to have a strong and potent health benefit for cardiac patients, and may eventually results in sustained effect on physical and mental health outcomes.

### **10.4 Compensation for injury**

DIAGRAM maintains appropriate clinical trial liability insurance coverage as required under applicable laws and regulations and will comply with applicable local law and custom concerning specific insurance coverage. All patients participating in the study are insured against damages according to the regulation.

## 11. ADMINISTRATIVE ASPECTS, MONITORING AND PUBLICATION

### 11.1 Handling and storage of data and documents

Electronic Case Report Forms (eCRFs) have been developed to capture the study information outlined in this protocol. Data from these eCRFs will be used in the analysis of study results. Modification of the eCRFs will only be made if deemed necessary by the principal investigator.

All centre personnel will be trained on the protocol and internet-based database eCRF prior to the initiation of the study. Trained and qualified Clinical Research Associates (CRAs) of Diagram and/or his designee will monitor the trial throughout its duration by means of personal visits to the physician's facilities, telephone contacts to the physician or designee, and/or remotely through the internet-based database. A comprehensive, integrated data management plan, including on-line queries and remote data cleaning will be implemented to insure the integrity of the data. All changes to the database will be tracked by an audit trail.

The site investigator, or a designated individual, is responsible for recording all data from the study on the eCRFs based on source-documented hospital chart reviews at his/her centre. The site investigator is required to electronically sign the eCRF on the appropriate pages to verify that he/she has reviewed and attests to the correctness of the recorded data.

All eCRFs should be thoroughly completed within 30 days after the study staff study specific information. For adverse event reporting, refer to section on Adverse Event Reporting Requirements and timelines (see paragraph 7.2).

Data entered in to the eCRFs will be taken from source documentation, such as hospital procedure reports, admission and discharge summaries and other hospital or physician office/clinic documents. If no standard hospital or office document exists to capture some of the information that may be unique to this study, a worksheet may be developed to record this information, which needs to be signed by the site investigator at the given centre, and which will serve as the source document for those data parameters. These source documents will serve as the basis for monitoring the eCRFs. Electronic patient records will be considered as source documents on the condition that the hospital's database is a validated system. If this is not the case, electronic records will have to be printed and added to the paper patient file. A print-out of the eCRF cannot be used as source documentation.

The site investigator will maintain all records pertaining to this study for fifteen years following study completion, or as otherwise instructed by the CRO, or per local requirements whichever is longer.

## **11.2 Monitoring and Quality Assurance**

Source data verification will be done completely for at least the first five included patients per centre and 10% of the other included patients. For the other included patients at least informed consent and reported endpoints will be checked by the CRA. The site investigator will permit access to such records. Source documentation must be available to substantiate proper informed consent procedures, adherence to protocol procedures, adequate reporting and follow-up of adverse events, accuracy of data collected on case report forms, and device information. A monitoring visit sign-in log will be maintained at the centre. The site investigator and/or research coordinator will be available for monitoring visits. It is expected that the site investigator will provide the study monitor with a suitable working environment for review of study-related documents.

### **Investigators Responsibilities**

The site investigators at the clinical centre will have the following responsibilities:

- Obtaining approval from the Medical Ethics Committee
- Obtaining written informed consent from patients
- Adequate enrolment of patients
- Performing medical procedures
- Adherence to the clinical protocol
- Following patients according to the protocol

### **Protocol Compliance**

The site investigator is responsible for monitoring compliance with the clinical investigation protocol. The CRA will perform visits to inspect and audit study files and regulatory documentation, including site investigator and co-investigator curricula vitae, Ethics Committee approval documentation, patient informed consent forms and study correspondence logs. When problems are identified, assistance will be given to the appropriate individuals to ensure consistency of data collection procedures and transmission of data forms to the investigator. The site investigator will verify that the data recorded on the procedure forms are correct through review of reports and medical records. CRA and/or designee will monitor the study over its duration according to the pre-specified monitoring plan. The CRA will visit each centre at appropriate intervals to review investigational data for accuracy and completeness and ensure compliance with the protocol. The CRA may inspect all documents and required records that are maintained by the site investigator, including medical records (office, clinic or hospital) for the subjects in this study. The site investigator will permit access to such records. Source documentation must be available to substantiate proper informed consent procedures,

adherence to protocol procedures, adequate reporting and follow-up of adverse events, accuracy of data collected on case report forms, and device information. A monitoring visit sign-in log will be maintained at the centre. The site investigator and/or research coordinator will be available for monitoring visits. It is expected that the site investigator will provide the study monitor with a suitable working environment for review of study-related documents.

